## Abstract

**Background:**

FangJiHuangQi Granules (FJHQG) is a Chinese patent medicine that alleviates heart failure (HF) symptoms derived from the formula FangJiHuangQi decoction. Previous experiment has revealed that FangJiHuangQi decoction alleviated pathological injury in rats with HF. This trial intends to evaluate FJHQG's efficacy and safety as a complementary therapy in addition to conventional drug treatment.

**Methods:**

This trial is a randomized, double-blind, placebo-controlled study that recruits 100 patients with HF. Participants will be randomly assigned into the intervention and control groups (*n* = 50 for each group). For a duration of 12 weeks, FJHQG will be administered to the intervention group, and the control group will receive standard therapy plus placebo. The primary outcome of the trial is the changes of six-minute walk test at week 24. Secondary outcomes include BNP levels, NYHA classification, major adverse cardiovascular events (MACE), and KCCQ quality of life scales. Other exploratory assessments at the beginning and after a 12-week period will include fluid balance, symptom score scales, echocardiograms, diuretic consumption, and biochemical indices. Monitoring of MACE will continue until 12 weeks after drug discontinuation.

**Discussion:**

This study will evaluate the efficacy and safety of FJHQG in HF treatment and to examine potential mechanisms, offering new insights into HF treatment.

**Clinical Trial Registration:**

ChiCTR.org, ChiCTR2400080029.

## Introduction

1

Heart failure (HF) is a complicated medical disorder triggered by multiple elements that cause detrimental modifications in cardiac structure and functionality. HF affects more than 64 million people worldwide (1). In industrialized countries, heart failure typically affects about 1% to 2% of adults, causing a heavy symptom and economic burden worldwide (2). Consequently, there is an immediate need to develop new drugs to reduce clinical event risks in patients with HF.

HF is often treated with Traditional Chinese Medicine (TCM) because of proven efficacy in ameliorating symptoms. According to TCM theory, HF mainly arises from a deficiency of heart Qi and blood stagnation. This condition denotes a pathological state wherein Qi is unable to facilitate effective blood circulation, leading to impaired or stagnant blood flow. Clinically, heart Qi deficiency usually manifests as fatigue, shortness of breath, palpitations, and impaired exercise tolerance, reflecting insufficient cardiac driving force. Blood stasis is associated with chest tightness or pain, and cyanosis of the lips, indicating impaired blood circulation. Water stasis results from an inability of Qi deficiency and blood stasis to regulate fluid metabolism and is typically manifested by peripheral edema, orthopnea, abdominal distension, and reduced urine output, which are typical symptoms of HF. The FangJi HuangQi (FJHQ) decoction, a renowned prescription in TCM comprises the following Chinese medicinal ingredients: *Astragalus membranaceus* (Fisch.) Bge. (6 g), *Stephania tetrandra* S. Moore (1.5 g), *Atractylodes macrocephala* Koidz*.* (3 g), *Glycyrrhiza uralensis* Fisch. (1 g), *Lepidium apetalum* Willd. (2.5 g), *Prunella vulgaris* L. (3 g), and *Salvia miltiorrhiza* Bunge (4 g). This formulation is reputed for its ability to “reinforce qi and improve blood circulation, invigorate spleen function, and clear water”. Extensive preliminary research has demonstrated that the herbs in the FJHQ decoction are both safe and effective (3, 4). Moreover, toxicological evaluations in rats revealed no noticeable negative impacts on the central nervous, respiratory, or cardiovascular systems, thus confirming the compound's safety (5, 6). In rats with pulmonary artery hypertension, the FJHQ decoction improved hemodynamic parameters, enhanced lung function, and lessened pulmonary vascular remodeling (7). In addition, FJHQ decoction has shown its effects in several cardiovascular conditions including hypertension, myocardial ischemia, and cardiac fibrosis (8). It has been shown that FJHQ decoction effectively improved exercise capacity and reduced diuretic usage and resistance without significant liver or kidney damage or adverse events in small-scale clinical observations (9, 10). However, there is still a lack of clinical evidence regarding the effectiveness and safety of FJHQ decoction in patients with HF.

FJHQ decoction has been applied in clinical practice for over a thousand years. However, the preparation of traditional decoctions is often time-consuming and complicated. Compared with traditional decoctions, the granule formulation provides improved quality consistency, enhanced reproducibility, and better patient compliance due to its convenience, making it more suitable for use in randomized controlled trials. Hence, this study will assess the efficacy and safety of FangJiHuangQi granule (derived from the FJHQ decoction, with the same ingredient and proportion, FJHQG) in patients with HF. Moreover, we plan to explore the potential mechanisms of FJHQG in patients with HF.

## Methods/design

2

### Study design

2.1

This trial is a part of the project “Theoretical Research on Treating HF with TCM Compatibility Formula - Topic Five Group Distribution Combination Theory Research” (2018 YFC1704505), led by Tianjin University of Traditional Chinese Medicine. The Hangzhou Hospital of Traditional Chinese Medicine, acting as the appointed clinical trial unit, hosts the clinical trial. The investigation will be conducted in accordance with Good Clinical Practice standards and the ethical principles of the Helsinki Declaration (11, 12). The research will follow the SPIRIT guidelines for interventional trials (13). Additionally, it will strictly adhere to the guidelines set forth by the 2017 CONSORT-CHM Formulas for Chinese Herbal Medicine (14).

This is a randomized, double-blind, placebo-controlled trial. The study will take place at Hangzhou Hospital of TCM and will include two stages: a 12-week treatment phase and a subsequent 12-week follow-up phase after intervention. A total of 100 patients with HF will be randomly assigned to two groups equally. On the basis of conventional drug therapy, the intervention group will receive treatment with FJHQG, while the placebo group will receive the corresponding placebo of FJHQG. Figure 1 depicts the study design.

**Figure 1 F1:**
[figure not shown]
Flow diagram of the study.

### Diagnostic criteria

2.2

The criteria for diagnosing HF follow the “2018 Chinese Guidelines for Heart Failure Diagnosis and Treatment Guideline” (15). The diagnostic criteria were defined according to the guidelines in effect at the time of study initiation and ethical approval.

The diagnosis of the TCM syndrome Qi deficiency, blood stasis, and water retention was based on the Technical Guidelines for Clinical Research of Traditional Chinese Medicine New Drugs in Chronic Heart Failure.
1.Qi deficiency and blood stasis syndromeMajor symptoms include: (1) shortness of breath or dyspnea; (2) fatigue; (3) palpitations. Secondary symptoms included: (1) general weakness and reluctance to speak; (2) spontaneous sweating; (3) low voice; (4) dark or purplish complexion or lips. Tongue and pulse signs included a dark tongue (with or without petechiae or ecchymosis, or engorged sublingual veins), thin white coating, and a deep, thready, uneven pulse or weak pulse. Diagnosis is established when at least two major symptoms and two secondary symptoms are present, combined with tongue and pulse manifestations.
2.Water retention syndromeSymptoms include: (1) cough or sputum; (2) chest fullness or abdominal distension; (3) facial or limb edema; (4) oliguria. Tongue and pulse signs included a moist or greasy tongue coating or a slippery pulse. Diagnosis is established when at least one symptom is present, combined with tongue and pulse manifestations.

### Inclusion criteria

2.3

The study will include participants who satisfy all of the following inclusion criteria:
Diagnosis of chronic heart failure in a stable condition (defined as no acute decompensation, and no hospitalization for heart failure within at least 2 weeks before randomization), classified as heart failure with mildly reduced ejection fraction (LVEF: 41%–49%) or heart failure with preserved ejection fraction (LVEF≥50%), with BNP ≥35 pg/mL, and at least one of the following echocardiographic features present: left ventricular hypertrophy and/or left atrial enlargement; diastolic dysfunction, according to the 2018 Chinese Guidelines for the Diagnosis and Treatment of Heart Failure, and meeting the criteria of “Qi deficiency, blood stasis, and water stasis” syndrome;Patients must be on stable guideline-directed medical therapy for heart failure prior to randomization, defined as no major changes in medications within at least 2 weeks;NYHA classification of II to III;Age between 18 and 80 years;Voluntary acceptance the medication treatment and provision of an informed consent form trained investigators.

### Exclusion criteria

2.4

Participants will be excluded if they meet any of the exclusion criteria:
Unmanaged high blood pressure, defined by a resting systolic pressure of 180 mmHg or more, or a diastolic pressure of 110 mmHg or above, confirmed by two separate measurements before randomization;Presence of acute coronary syndrome, recent or planned vascular revascularization within the past month or upcoming week, cardiogenic shock, life-threatening arrhythmias, myocarditis, constrictive pericarditis, pulmonary embolism, or other similar conditions;Autoimmune conditions, including systemic lupus erythematosus and giant cell myocarditis;Life-threatening conditions, including malignant tumors, or poorly controlled mental illnesses, as well as drug abuse;Severe liver or kidney impairment, characterized by alanine aminotransferase levels at least three times the normal maximum or creatinine levels of 3 mg/dL or higher;Known allergy to the medication being studied or any of its ingredients is known.Women who are planning to become pregnant, are currently pregnant, breastfeeding, or not utilizing effective contraception during the trial period;Involvement in additional clinical studies during the designated period.

### Withdrawal, dropout, and discontinuation

2.5

The study will allow participants to withdraw at any point if: (1) the intervention threatens participants' safety; (2) a significant adverse reaction is observed; (3) the participant does not comply with the protocol. The reason for withdrawal will be documented in detail.

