### Intervention

2.7

Every participant will be treated following the “2018 Chinese Guidelines for Heart Failure Diagnosis and Management” (15). This therapeutic plan involves diuretics, angiotensin-converting enzyme inhibitor (ACEI), angiotensin receptor blocker (ARB), angiotensin receptor-neprilysin inhibitor (ARNI), beta-blockers, and other suggested treatments. Optimal medical management will be ensured in alignment with the guidelines. All background medication will follow guideline-directed medical therapy. All concomitant medications and treatment adjustments during the study will be recorded in detail, and potential between-group differences will be summarized and adjusted. In addition, the intervention group will be given FJHQG, while the control group will undergo conventional drug therapy and corresponding placebo, both for a duration of 12 weeks. FJHQG is manufactured by CHIATAI QINGCHUNBAO PHARMACEUTICAL Co., Ltd. in accordance with Good Manufacturing Practice standards. All study medications will be provided by the manufacturer in standardized packaging. To ensure traceability, batch numbers will also be recorded (batch number: 2308702). The placebo will be identical to FJHQG in appearance, taste, and packaging to maintain blinding. Participants will be instructed to consume the granules (5 g per dose, twice daily). To guarantee adherence, the granules will be handed out and/or gathered during every visit. Adherence will be assessed based on sachet counts and patient-reported intake and will be calculated as the proportion of sachets taken relative to the total number prescribed. Missed doses and treatment interruptions will be recorded, and adherence below 80% will be considered a protocol deviation. During the trial, the use of other traditional Chinese medicine that may affect diuretic function is strictly prohibited.

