### Follow-up visits and monitoring schedule

2.8

The study will start with a 7-day preliminary phase where eligible individuals will provide their consent and initial information will be gathered. Future appointments will be planned for 6 days ± 1 day (visit 1), 4 weeks ± 3 days (visit 2), and 12 weeks ± 3 days (visit 3) after starting the treatment. Follow-up assessments will be conducted at Week 12 ± 7 days post-discontinuation of treatment (24W ± 7d) (visit 4). To minimize loss to follow-up, participants will be regularly contacted through telephone calls and WeChat group communication. Reminders will be provided before each scheduled visit to improve retention and adherence. Table 1 outlines the comprehensive assessment timetable.

**Table 1 T1:** Schedule of enrollment, interventions, and assessments.

Study phase time	Lead-in period	Treatment period			Follow-up period
	Screening (−7D-0D)	Baseline (6D ± 1d)	Week 4 (4W ± 3d)	Week 12 (12W ± 3d)	Week 24 (24W ± 7D)^a^
Patients					
Eligibility screen	X				
Inclusion/exclusion criteria	X				
Informed consent	X				
General information	X				
Medical history	X				
Allocation	X				
Pregnancy examination	X				
Outcomes					
Primary outcome					
6-minute walk test	X	X	X	X	X^c^
Secondary outcomes					
BNP	X	X	X	X	X
MACE (including cardiac death, non-fatal myocardial infarction, and rehospitalization due to heart failure) ^b^	X	X	X	X	X
NYHA classification	X	X	X	X	X
KCCQ quality of life score	X	X	X	X	X
Exploratory outcomes					
Diuretic usage		X	X	X	X
Echocardiography	X			X	X
Heart failure-related rehospitalization rate^b^	X	X	X	X	X
TCM syndrome score	X	X	X	X	X
Myocardial enzyme levels	X			X	X
Inflammatory markers and other biochemical indicators	X			X	X
Safety					
Vital signs	X	X	X	X	X
Biochemical indexes	X			X	X
Electrocardiogram results	X			X	X
Adverse events	X	X	X	X	X
Others					
Drug distribution	X		X		
Drug recycle			X	X	
Combined medication			X	X	
Confirmation of medication compliance		X	X	X	X

a Visit 4 corresponds to the follow-up assessment conducted at Week 24, which is 12 weeks after completion of the 12-week treatment period, as stated in manuscript.

b Continuous monitoring throughout the study.

c Primary endpoint assessed at week 24.

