### Outcomes

2.9

The primary outcome of the trial will be the variation in the 6-minute walk test by week 24 as compared to baseline. The assessment of 6MWT will be performed in accordance with standardized procedures. The test will be conducted in a 30-meter corridor, and standardized instructions and encouragement will be provided to all participants. To ensure patient safety and consistency, predefined stopping criteria including intolerable dyspnea, chest pain, dizziness, or any other symptoms indicating potential risk, as judged by the assessor, will also be applied. The use of walking aids or supplemental oxygen will be permitted if clinically necessary, and the use will be recorded to minimize variability. Moreover, all outcome assessors will remain blinded to treatment allocation throughout the study to reduce measurement bias. The same assessor will evaluate a given participant across study visits to reduce inter-rater variability. All assessors will receive standardized training prior to study initiation. The 6MWT will be performed 1–2 h after routine medication administration to minimize variability. Duplicate tests will not be performed unless clinically indicated.

The secondary outcomes will include: (1) major adverse cardiovascular events (MACE, including cardiac death, non-fatal myocardial infarction, and rehospitalization due to HF) at 3 and 6 months. All major adverse cardiovascular events and heart failure-related rehospitalizations will be reviewed and adjudicated by an independent committee blinded to treatment allocation; (2) BNP levels at week 24 compared with baseline; (3) NYHA class functional classification at week 24 compared with baseline; (4) quality of life score of the Kansas City Cardiomyopathy Questionnaire at week 24 compared with baseline.

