### Statistical analysis

2.15

All statistical analyses will be conducted on both the intention-to-treat (ITT) and per-protocol (PP) populations. The ITT population will include all randomized participants, while the PP population will consist of participants with at least 80% adherence to the protocol. Continuous variables following a normal distribution will be presented as means ± standard deviations (SD) with 95% confidence intervals (CI), and non-normally distributed variables will be reported as medians with interquartile ranges (IQR) and analyzed using non-parametric methods. Between-group comparisons for normally distributed continuous variables will use the independent samples t-test, and for non-normal distributions, the Wilcoxon rank-sum test. Within-group comparisons will employ paired t-tests or Wilcoxon signed-rank tests as appropriate. Categorical variables will be summarized as counts and percentages, with between-group comparisons using the Chi-square or Fisher's exact test, and within-group comparisons using the McNemar test. Baseline characteristics will be reported descriptively without significance testing to assess comparability between groups. Differences in background treatment between groups will be summarized descriptively and adjusted for in the statistical analysis to reduce potential confounding.

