The primary outcome (6-minute walk test) will be analyzed using analysis of covariance (ANCOVA) with baseline values and key covariates (age, sex) as covariates to adjust for potential confounding. Secondary outcomes, due to their diverse nature, will be analyzed using appropriate methods: continuous variables with t-test or Wilcoxon test, categorical variables with Chi-square or Fisher's exact test, and repeated measures or longitudinal data using linear mixed-effects models. To control for multiple comparisons among secondary outcomes, the false discovery rate (FDR) adjustment using the Benjamini-Hochberg method will be applied, and a hierarchical structure will be applied with the primary outcome taking precedence over secondary and exploratory outcomes. The primary analysis will be conducted according to the intention-to-treat (ITT) principle, including all randomized participants. If the proportion of missing 6MWT data is 5% or greater, missing data for the 6MWT will be handled using multiple imputation under the missing-at-random assumption. The imputation model will include baseline 6MWT value, age, sex, and treatment group as predictors. Imputation will be performed using a single model based on all available data without separating treatment arm. In addition, reasons for missing data will also be recorded, categorized, and summarized descriptively, and will be compared between groups. Prespecified subgroup analyses will be conducted based on heart failure phenotype, defined by left ventricular ejection fraction (LVEF ≥50% vs. <50%), and by sex. These subgroup analyses will be considered exploratory. Sensitivity analyses will be performed, including per-protocol analyses and complete-case analyses, to assess the robustness of the results. Deaths occurring before the final assessment will be handled in sensitivity analyses using a worst-case approach by assigning a value of zero for the 6MWT, representing the worst functional outcome. Adverse events will be summarized in tables and compared between groups using descriptive statistics. All analyses will be performed using SAS software version 9.4, and two-tailed *P*-values < 0.05 will be considered statistically significant. A detailed statistical analysis plan will be finalized prior to database lock to ensure prespecified analysis procedures.

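### Section 2.5 makes non-compliance a ground for leaving the study, which conflicts with an ITT primary analysis that needs week-24 walk distances from non-adherent participants

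*Protocol article*

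**What the plan says.** **Section 2.5 (Withdrawal, dropout, and discontinuation).** The rule opens "The study will allow participants to withdraw at any point if: (1) the intervention threatens participants' safety" and then adds a significant adverse reaction as the second ground and non-compliance as the third: "3) the participant does not comply with the protocol". On what is recorded, it says only "The reason for withdrawal will be documented in detail".

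**Section 2.7 (Intervention).** Adherence is the share of prescribed sachets taken, and "adherence below 80% will be considered a protocol deviation". Nothing there makes low adherence a reason to leave.

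**Section 2.9 (Outcomes).** "The primary outcome of the trial will be the variation in the 6-minute walk test by week 24 as compared to baseline". Treatment lasts 12 weeks, so the endpoint falls 12 weeks after planned treatment ends.

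**Section 2.15 (Statistical analysis).** "The primary analysis will be conducted according to the intention-to-treat (ITT) principle, including all randomized participants". Beside it, "the PP population will consist of participants with at least 80% adherence to the protocol". If 5% or more of the walk-test data are missing, multiple imputation under missing-at-random is used, with baseline walk distance, age, sex and treatment group as predictors. The named sensitivity analyses are per-protocol, complete-case, and a value of zero for deaths.

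**The concern.** The same participant is handled in two ways. Someone who takes fewer than 80% of the sachets is a retained protocol deviation under section 2.7, and belongs to the ITT set but not the per-protocol set under section 2.15. Under section 2.5 that person may instead be withdrawn from the study. Site staff cannot tell from the text which rule applies, or whether a participant withdrawn on the third ground is still invited to the week-24 visit.

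At stake is the observed primary outcome in people who did not take the treatment as planned. An ITT comparison of all randomized participants needs those values. A participant who leaves during the 12 treatment weeks has at least 12 further weeks to go before the primary assessment, so leaving follow-up would normally mean losing it. The loss would be avoidable, because the visit is already scheduled, and it could not be repaired at the analysis stage.

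**Working it through.** **1. The plan's own figure.** Section 2.14 assumes a 50 m difference, SD 72 m, two-sided alpha 0.05 and 90% power. A two-sample t-test gives 44.56, so 45 per group. Allowing 10% dropout, 45 / 0.90 = 50 per group, 100 in total. The stated sample size reproduces and is not in dispute.

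**2. The rules side by side, for a participant below 80% adherence.**

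| Section | Status of this participant |
|---|---|
| 2.5 | May be withdrawn from the study; reason recorded; later outcome collection neither required nor ruled out |
| 2.7 | Protocol deviation |
| 2.15, ITT | Included in the primary analysis |
| 2.15, per-protocol | Excluded |

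The last three rows fit together. The first does not, unless withdrawal there leaves outcome collection running, which the text does not say.

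**3. What happens to a lost value.** The listed imputation predictors do not include adherence, withdrawal reason, or the walk tests that Table 1 schedules at weeks 4 and 12. The lost value is therefore predicted from participants with observed week-24 data, given baseline distance, age, sex and arm. Complete-case analysis leaves out anyone without a week-24 value, and per-protocol analysis leaves out anyone below 80% adherence. The zero rule covers deaths only. None of these asks what follows if the lost participants differ from those used to impute them.

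**4. Possible size of the bias.** Let f be the share of an arm withdrawn for non-compliance and lost. Let D be how many metres worse their true mean change is than that of otherwise similar retained participants. Imputation then sets that arm's mean about f × D too high, and the bias in the difference (FJHQG minus placebo) is about

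f(FJHQG) × D(FJHQG) − f(placebo) × D(placebo).

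The documents give neither f nor D, so both are assumptions:

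| Loss, one arm only | D = 30 m | D = 50 m |
|---|---|---|
| f = 10% | 0.10 × 30 = 3 m | 0.10 × 50 = 5 m |
| f = 20% | 0.20 × 30 = 6 m | 0.20 × 50 = 10 m |

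- Loss on FJHQG only: the difference is overstated by these amounts.
- Loss on placebo only: it is understated by the same amounts.
- Equal f and equal D in both arms: f × D − f × D = 0.

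**5. Scale.** Losing 10% of one arm is 5 of 50, or 5 of 100 overall, which is the 5% at which imputation starts. Losing 20% of one arm is 10 of 100 overall, equal to the whole anticipated dropout. Section 2.14 calls about 30 m clinically meaningful, so the top of the range is 10 / 30, one third of that; the bottom is 3 / 30, one tenth.

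**The case against.** The strongest reply is that section 2.5 is permissive. It allows withdrawal; it does not order non-compliers out, and it does not say that data collection stops. Sections 2.7 and 2.15 point to retention, and section 2.8 plans calls, reminders and WeChat contact to limit loss. Participants without a value remain in the ITT analysis through imputation. The article also condenses a fuller protocol, where follow-up after stopping drug may be spelled out.

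Much of this stands. A reader might infer that non-compliers are removed and their data discarded, or that the ITT set shrinks to nearly a per-protocol set; the documents support neither. What survives is that section 2.5 states a rule, not merely an omission, and that this rule conflicts with two others in the same article.

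Three further inferences are tempting and should not be drawn.

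- **That the bias favours FJHQG.** The trial is double-blind with a matched placebo. Withdrawal for lack of effect could be commoner on placebo, which would push the other way.
- **That a definite amount of power is lost.** No rate of withdrawal for non-compliance is given, and nothing says such withdrawals fall outside the 10% allowance.
- **That early stoppers would have their primary assessment before week 24.** Section 2.8 says "Follow-up assessments will be conducted at Week 12 ± 7 days post-discontinuation of treatment (24W ± 7d) (visit 4", which read alone could move the visit for someone who stops early. But the week-24 window stands in the same sentence, Table 1 and its footnotes fix week 24, and so does section 2.9. At most the wording needs tidying.

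**Conclusion.** The point holds as an inconsistency between stated rules that puts outcome data at risk. Non-compliance without a threshold is a ground for leaving the study in section 2.5, while sections 2.7 and 2.15 need the same people to stay and be measured. If section 2.5 is applied so that follow-up ends, the lost week-24 distances are imputed from a short list of baseline predictors and arm, and no named sensitivity analysis tests that step.

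The size is uncertain: about zero under balanced loss, and about 3 to 10 m in either direction under one-arm loss of 10 to 20% with outcomes 30 to 50 m worse. Those inputs are assumed. The range also rests on adherence-related differences not already explained by baseline distance, age, sex and arm. That missingness will be related to response is a plausible risk, not something the article states. The sample size needs no change on this account.

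**What to change.** Reconcile section 2.5 with sections 2.7 and 2.15:

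1. Separate discontinuation of study drug from withdrawal from the study.
2. State that non-compliance, or stopping the granules, does not by itself end follow-up.
3. State that the scheduled week-24 6-minute walk test is sought from every randomized participant who has not withdrawn consent, where it can safely be done, and that the result is used in the ITT analysis.
4. In section 2.8, word Visit 4 as week 24 for everyone.

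The two safety-related grounds in section 2.5, the drug-stopping criteria in section 2.10 and clinical judgement about performing the walk test stay as they are.

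The cost is a change of wording, plus some visits by participants who are off drug. Those visits are already in the schedule.
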